### Outcome evaluation

The baseline questionnaire contains 19 questions about sociodemographic data and smoking habits. The participants will be asked to state their age, gender, marital status and years of smoking and, if using Swedish snuff (‘*snus*’), how much per day. Then follows the 6 questions of Fagerström’s Nicotine Dependence Scale and a question on how important it is for the participants to quit smoking with response option on a scale from 1 to 10, where 1 stands for not important at all and 10 very important. All participants will be asked if they ever have tried to stop smoking before (and if so how many times); if they ever have tried nicotine replacement (if so how many times); if they have been prescribed drugs for smoking cessation, and if they have received professional counselling or if they have called the national quit smoking help-line.

After 4 months, a link to an electronic follow-up questionnaire will be Emailed to all participants. Initially, 2 reminders 1 week apart will be sent to non-responders. In order to minimise attrition those participants still not responding will receive additional Email reminders every second day for 6 days (that is 3 Emails). If still not responding, the non-responders will receive a SMS every second day for 6 days (that is 3 SMS) with only 2 questions to answer, to capture the 2 primary outcome measures. Lastly, those still not responding will be phoned with a maximum of 10 calls per participant. Also, in the invitation to answer the follow-up questionnaire the participants will be told that they are offered the opportunity to be part of a draw for a number of iPads (Apple Inc., Cupertino, CA, USA) after having answered the follow-up questionnaire.

Outcome measures are as follows:

*Primary outcome measures*:Self-reported prolonged abstinence (defined as having not smoked more than 5 cigarettes in the last 8 weeks).Self-reported 4-week point prevalence of smoking abstinence (not having smoked a single cigarette).

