#### Primary analyses

The primary analyses will assume that missing outcome data are missing at random and, therefore, will be performed on complete cases only.

The binary outcomes of self-reported prolonged abstinence, 4-week prevalence of smoking abstinence and 7-day point prevalence of smoking abstinence will be analysed by logistic regression and results presented as odds ratio (95% CI). Number of quit attempts and number of uses of other smoking cessation services will be analysed by negative binomial regression and results presented as ratio of means (95% CI). Numbers of cigarettes smoked weekly will be analysed by logarithmic transformation and linear regression and results presented as ratio of geometric means (95% CI).

All regression analyses will be adjusted for by the following baseline variables: gender, years of smoking, average number of cigarettes smoked weekly, severity of dependence as measured by Fagerström’s Nicotine Dependence Scale and amount of ‘*snus*’ used at baseline.

Effect modification analyses will be performed for the two primary outcomes and the following potential effect modifiers measured at baseline: gender, average number of cigarettes smoked weekly, amount of ‘*snus*’ used weekly, and severity of dependence as measured by Fagerström’s Nicotine Dependence Scale. Each effect modification will be assessed by adding the appropriate interaction term to the adjusted regression model. Consideration for adjustment for multiplicity of comparisons will be discussed. All tests will be performed 2-sided with a 5% level of significance.

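### The count models for quit attempts and use of other cessation services leave out the related baseline histories, at some cost in precision and robustness on two secondary outcomes

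*Protocol article*

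**What the plan says.** The Data analysis section says that the analysis will follow the plan set out beneath it, so the covariate list is a decision taken in this document. Under Primary analyses the list reads: "All regression analyses will be adjusted for by the following baseline variables: gender, years of smoking, average number of cigarettes smoked weekly", then "severity of dependence as measured by" the Fagerström scale, and the amount of snus. It holds for every regression: logistic for the three abstinence outcomes, negative binomial for quit attempts and for uses of other cessation services, and linear on the log scale for weekly cigarettes.

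Under Outcome evaluation, the baseline questionnaire is described as collecting more than this:

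- earlier quit attempts: "if they ever have tried to stop smoking before (and if so how many times";
- nicotine replacement: "if they ever have tried nicotine replacement (if so how many times";
- prescribed drugs: "if they have been prescribed drugs for smoking cessation";
- professional counselling and calls to the national help-line, with no count described;
- motivation: "a question on how important it is for the participants to quit smoking with response option on a scale from 1 to 10".

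None of these is in the list. Missing outcomes are assumed missing at random (MAR), and the primary analyses use complete cases.

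**The concern.** Of the three non-binary outcomes, only weekly cigarettes has its baseline counterpart in its own model. The other two are counts whose related histories are collected and then not used, and the article gives no reason for the difference. A prognostic baseline variable in a count model can absorb part of the overdispersion and so narrow the interval for the ratio of means.

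Missing data make this more relevant for the counts than for abstinence. Non-responders who answer at the SMS stage are asked only the two primary questions, so they supply no counts. The methods described under Sensitivity analyses are built around abstinence: the informatively missing odds ratio (IMOR) is an odds ratio, and the worked example is a proportion abstinent. As described, the MAR assumption for the counts therefore rests mainly on the covariates in the model. At stake are the precision and robustness of the results for hypotheses 4 and 5.

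**Working it through.** **1. The plan's own figure.** The sample size uses 10% v 5%, two-sided 0.05, 80% power and a continuity correction.

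- Uncorrected: n = [1.96√(2 × 0.075 × 0.925) + 0.8416√(0.10 × 0.90 + 0.05 × 0.95)]² / 0.05² = 434.4, that is 435.
- Corrected: (434.4/4) × [1 + √(1 + 4/(434.4 × 0.05))]² = 473.6, that is 474, as stated.
- Attrition: 474/0.70 = 677.1, against the stated 677 (678 if rounded up).

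None of this depends on the covariates, so the sample size is unaffected.

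**2. Outcome against baseline item.**

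| Outcome | Related baseline item collected | In its model? |
|---|---|---|
| Cigarettes per week | average weekly cigarettes | yes |
| Quit attempts since joining | number of earlier attempts | no |
| Uses of other services since first invitation | nicotine replacement (with count), prescribed drugs, counselling, help-line | no |

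**3. Precision of the count models.** For a negative binomial outcome with mean μ and overdispersion k in each arm, approximately

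Var(log ratio) = 2(1/μ + k)/n.

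If the added history explains a share s of the overdispersion left after the five listed covariates, k becomes k(1 − s). The Poisson part 1/μ does not change. The ratio of standard errors is then

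√[(1/μ + k(1 − s)) / (1/μ + k)],

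in which n cancels. The documents give none of μ, k or s, so all three are assumptions.

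| μ | k | s = 10% | s = 25% | s = 50% |
|---|---|---|---|---|
| 1 | 0.5 | 0.983 | 0.957 | 0.913 |
| 1 | 1.0 | 0.975 | 0.935 | 0.866 |
| 2 | 0.5 | 0.975 | 0.935 | 0.866 |
| 2 | 1.0 | 0.966 | 0.913 | 0.816 |

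Example: for μ = 1, k = 0.5, n = 474 and s = 25%, the standard error falls from √(2 × 1.5/474) = 0.0796 to √(2 × 1.375/474) = 0.0762.

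The standard error therefore falls by about 2–3%, 4–9% or 9–18% for s of 10%, 25% or 50%. Over s of 10–25%, the equivalent gain in participants runs from 1.5/1.45 = 1.03 to 1.5/1.25 = 1.20, that is about 3 to 20%.

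**4. Does the same hold for abstinence?** In 2,000 simulated trials of 474 per arm at 10% v 5%, logistic regression was run with and without a standard-normal importance score. The five planned covariates were left out for simplicity.

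| Assumed OR per SD of importance | SE of log OR without / with | Power without / with |
|---|---|---|
| 1.2 | 0.264 / 0.265 | 85.2% / 85.1% |
| 1.5 | 0.264 / 0.266 | 83.7% / 83.9% |
| 2.0 | 0.264 / 0.270 | 85.2% / 86.0% |

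The standard error does not fall, and power moves by at most about 1 point.

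**5. MAR for abstinence.** Complete-case logistic regression was run on 1,000,000 simulated participants with about 30% missing.

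- *Importance predicts response equally in both arms (OR 1.5 per SD).* Omitting importance leaves the treatment odds ratio essentially unchanged, for example 2.09 against 2.08 in the full data.
- *The link differs by arm (1.0 v 1.5, in either direction).* For importance ORs of 1.2, 1.5 and 2.0, the odds ratio becomes 2.16, 2.18 and 2.29 one way, and 2.09, 1.99 and 1.96 the other. The full-data values are 2.11, 2.08 and 2.11. The shifts are about 1 to 9%; the smallest are no larger than the simulation noise. Including importance removes the shift apart from that noise.

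**The case against.** The strongest defence is that a short, pre-specified list is valid under randomisation. This one already holds consumption, dependence, years of smoking and snus. That stands, and it is why the point concerns efficiency and robustness only.

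A second defence is that the histories are only loosely matched to the outcomes. They are lifetime recalls, three of the service items have no count described, and the outcomes cover about four months. Every participant must also be willing to set a quit date within four weeks, and the intervention arm is given one by default. Lifetime history may therefore predict the counts weakly. This also stands, and it makes the lower part of the range at least as credible as the upper. A covariate need not share the outcome's time window to be prognostic, however.

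Stronger readings are tempting, but the documents do not support them:

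- *The primary outcomes lose precision.* A reader might extend the argument to abstinence. In the logistic models the standard error of the log odds ratio does not shrink when importance is added.
- *Simple randomisation leaves imbalance uncorrected.* Chance imbalance is already reflected in the confidence interval and the type I error rate, so it is not a bias.
- *The MAR analysis of abstinence is undermined.* Material bias needs importance to predict response differently by arm, which the article neither states nor implies. Departures from MAR are addressed by the IMOR range, the missing-equals-smoking analysis and the repeated attempts model. One gap remains: the IMOR is assumed equal in both arms, so that analysis does not vary the differential case.
- *The gain follows the rule 1 − r².* With an assumed r of 0.3 to 0.5, this would promise 10 to 33% more participants. It is a linear-model result and ignores the Poisson part of a count.

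**Conclusion.** The point holds as a minor one. Two secondary models omit related baseline information that the trial collects, while the third non-binary outcome has its own baseline value in the model. The likely cost is about 2 to 9% in the standard error of the log ratio, with 18% as an upper figure if history explains half the overdispersion. This rests on assumed means of 1 to 2, assumed overdispersion of 0.5 to 1 and an approximate variance formula. The benefit for missing data in the counts is sound in direction but has not been quantified.

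Validity, the sample size and the power of the two primary comparisons are not in question. For abstinence, the only case for adding importance is to make MAR more plausible if response depends on motivation differently by arm.

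**What to change.** Before follow-up data are opened, add to the list under Primary analyses:

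- **Quit attempts:** the number of previous quit attempts, in a form fixed in advance, since lifetime counts tend to be skewed.
- **Other cessation services:** one summary of earlier use, either an indicator of any use or the number of the four recorded services ever used. This adds one term instead of four.
- **Abstinence (optional):** a pre-specified sensitivity analysis that adds importance of quitting. It should be presented as a check on MAR. A small change in the odds ratio is expected even with complete data, because the adjusted odds ratio is conditional on one more variable (2.11 v 2.17 in the full simulated data at an importance OR of 2.0).

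The cost is a sentence or two and no new data. Each count model gains one term. With 474 × (0.10 + 0.05) = 71 expected events, the optional abstinence model goes from six terms to seven, or from about 12 to about 10 events per term. The gain may be small if lifetime history predicts four-month counts poorly. Participants with a blank history item would drop out of that model unless a rule for them is stated.

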### Objectives and hypotheses

The objective of the study is to evaluate the effectiveness of a SMS-based smoking cessation intervention. Participants in both the intervention and control group are told that they are free to seek any other treatment they want during the trial in the same manner as in previous studies [15-18].

Six hypotheses in total are being tested. The 2 primary hypotheses are that a greater proportion of participants in the intervention group than in the control group will report: 1) prolonged abstinence (8 weeks) and 2) recent abstinence (4 weeks) at follow-up. Secondary hypotheses are that the intervention group compared with the control group will report: 3) greater proportions of current abstinence (1 week); 4) a higher number of quit attempts; 5) greater use of other smoking cessation services; and 6) smoking fewer cigarettes among those still smoking at follow-up.

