### Sample size

Based upon previous studies, we expected an absolute difference in cessation rates between the intervention and control group of 5% (with 10% quitting in the intervention group and 5% in the control group) [15,20].

To achieve 80% power with a significance level of 0.05 (2-sided) and correction for continuity, a sample size of 474 persons is needed in each group. If there is 30% attrition in the follow-up measurement the number needed in each group is 677, with the total required sample size being 1,354. The allowance for attrition is deliberately conservative.

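### Two primary outcomes are each tested at 5% with no success rule or testing order; if either success counts, the chance of a false-positive primary result is about 7-9%

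*Protocol article*

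**What the plan says.** All references are to the protocol article.

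- *Objectives and hypotheses* states "Six hypotheses in total are being tested" and numbers two of them as primary: "The 2 primary hypotheses are that a greater proportion of participants in the intervention group than in the control group will report" prolonged abstinence (8 weeks) and recent abstinence (4 weeks).
- *Outcome evaluation* defines the two primary measures. The first allows up to 5 cigarettes over the last 8 weeks; the second allows none over the last 4 weeks.
- *Sample size* plans one comparison, 10% versus 5%, at a two-sided level of 0.05 with 80% power and a continuity correction. This gives 474 per group, and 677 per group (1,354 in total) after 30% attrition. It refers to cessation rates in general and does not say which primary outcome is meant.
- *Primary analyses* analyses both outcomes by logistic regression. The paragraph on effect modification ends with two sentences: "Consideration for adjustment for multiplicity of comparisons will be discussed" and "All tests will be performed 2-sided with a 5% level of significance".
- *Data analysis* presents what follows as the pre-specified statistical analysis plan and rules out interim analyses.

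**The concern.** With two primary hypotheses, a reader needs to know what counts as a positive trial: either outcome, both, or one ahead of the other. The article does not say. Each plain reading then breaks one of the design figures. If either success is enough, two tests at 5% give a false-positive chance above 5% for the trial's main claim. If both are needed, the error is controlled, but the 80% power, which was worked out for one comparison, no longer describes the chance of success.

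The gap matters because the two outcomes can disagree. A participant who smoked three cigarettes in the last month meets the first definition and not the second. One who stopped completely five weeks ago, after regular smoking, meets the second and not the first. If only one result is significant, the plan as written gives no answer on whether effectiveness has been shown.

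**Working it through.** **1. The plan's own figure.** Inputs from *Sample size*: p1 = 0.10, p2 = 0.05, two-sided alpha 0.05 (z = 1.960), power 80% (z = 0.842). The mean rate is 0.075 and the difference d is 0.05.

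- Without correction: n0 = [1.960·√(2·0.075·0.925) + 0.842·√(0.10·0.90 + 0.05·0.95)]² / 0.05² = 434.4, so 435 per group.
- With continuity correction: n = (n0/4)·[1 + √(1 + 4/(n0·d))]² = 473.6, so 474 per group. This matches the article.
- Attrition: 474/0.7 = 677.1, stated as 677; 2 × 677 = 1,354.

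So 474 is the size for one test at the full 5%.

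**2. Plausible correlation.** The article gives none, so this is an assumption. Both outcomes are measured in the same people at the same follow-up, and the 4-week window lies inside the 8-week window. For outcome rates a and b and joint rate ab, the correlation is (ab − a·b)/√[a(1−a)·b(1−b)]. Examples:

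- both rates 10%, and 90% of those with one outcome have the other: (0.09 − 0.01)/0.09 = 0.89;
- both rates 10%, 60% overlap: (0.06 − 0.01)/0.09 = 0.56;
- rates 10% and 15%, with 70% of the first group in the second: (0.07 − 0.015)/√(0.09·0.1275) = 0.51.

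A range of 0.5 to 0.9 is reasonable; 0.95 is shown as a stricter case.

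**3. Either outcome counts.** With bivariate normal test statistics of correlation r and no effect on either outcome, P(at least one significant) = 1 − P(|Z1| < 1.96 and |Z2| < 1.96).

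**4. Both outcomes required.** If each test alone has power π, joint power is P(Z1 < z_π and Z2 < z_π) at correlation r, where z_π is the normal quantile of π. This assumes 10% versus 5% on both outcomes. Two values of π are used: the stated 80%, and 83.3%. The second is the power at 474 per group without the continuity correction: Φ{[0.05 − 1.960·√(2·0.075·0.925/474)] / √[(0.10·0.90 + 0.05·0.95)/474]} = 0.833. It is shown because the planned logistic regression applies no such correction.

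| r | False positive, either counts | Joint power, each at 80% | Joint power, each at 83.3% |
|---|---|---|---|
| 0.5 | 9.1% | 69% | 73% |
| 0.7 | 8.3% | 71% | 76% |
| 0.9 | 7.0% | 75% | 79% |
| 0.95 | 6.5% | 76% | 80% |

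**The case against.** Several points on the other side are sound and limit what can be said.

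- **The 5% is a per-test level.** A reader might infer that a planned trial-wide error rate of 5% is broken. The article sets no family-wise target, and each test does keep its 5%. The defect is that the rate across the two primaries is left undefined.
- **Independence is not credible.** Two independent tests would give 1 − 0.95² = 9.75%. Overlapping abstinence windows in the same people are not independent, so that figure should not be used as the top of the range.
- **Timing is not stated.** A reader might infer that the decision on adjustment is deferred until the data are known. The article gives no time for the discussion. A fair reading is that tests are unadjusted and multiplicity is discussed in the report. A later choice of rule is something the wording permits, not something it announces.
- **The multiplicity sentence may be about the interaction tests.** It closes the paragraph on effect modification. If it is meant only for those tests, the article says nothing on multiplicity for the two primaries, and the gap is the same. A false-positive figure for the interaction tests has no bearing on the primary claim.
- **The continuity correction understates power.** This stands, and it is why both power columns are shown.

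It could also be said that a separate analysis plan may settle the matter. However, the article presents this section as the pre-specified plan, and it does fix the level for every test. The point therefore rests on what is stated here, not on a detail left elsewhere.

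**Conclusion.** The concern holds in a limited form. The article tests two primary outcomes at 5% each and does not say how their results combine into a conclusion. If either success supports the claim of effectiveness, the chance of at least one false-positive primary result is about 7-9% for correlations of 0.5 to 0.9, and 6.5% at 0.95. If both are required, there is no inflation, but joint power is about 69-75% with each test at 80%, or 73-79% without the continuity correction. At a correlation of 0.95 and without the correction it is about 80%.

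The correlation is an assumption throughout, and the power figures also assume the same 10% versus 5% effect on both outcomes. The inflation is moderate and depends on the either-success reading. It concerns the trial's main claim, however, and a success rule chosen once the results are known would carry little weight.

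**What to change.** State in the protocol and analysis plan, before follow-up data are analysed, that prolonged abstinence is tested first at two-sided 5%, and that 4-week abstinence is tested at two-sided 5% as confirmatory only if the first test is significant. Replace the open sentence on multiplicity with this rule so far as it concerns the primary outcomes. State also that the sample size calculation refers to prolonged abstinence.

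The order follows the article's own numbering. It holds the error across the two primaries at 5% without splitting the level, and 474 analysed per group (1,354 in total) remains valid for the first test. The change is to wording only and adds no participants. The cost is that 4-week abstinence cannot be claimed as confirmed if prolonged abstinence fails, however clear its own result.

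Other rules would also control the error. Requiring both outcomes has the joint power shown above. Halving the level to 0.025 per outcome gives about 71% power each at 474 per group (75% without the continuity correction). Relabelling the secondary outcomes or the interaction tests as exploratory is optional and is not needed to repair this point.

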#### Sensitivity analyses

Sensitivity analysis will explore the effects of departures from the missing at random assumption in the main analysis [37-40]. As suggested by Jackson *et al*. [39], we will quantify departures from the missing at random (MAR) assumption by the informatively missing odds ratio (IMOR). We will assume that the IMOR is the same in each randomised group and we will vary the IMOR over the range 0.5 to 1; if 10% of observed data are abstinent then this range implies that from 5% to 10% of missing data are abstinent. We will also allow the IMOR to be 0 (missing = smoking, the Russell standard) [41]. Further, we will use data on the number of follow-up Emails, texts and phone calls needed before an individual responded to explore the plausibility of the MAR assumption: first by exploring the association between quitting and number of follow-up attempts needed, and then by fitting the repeated attempts model of Jackson *et al*. [38,39] which will allow us to both estimate the degree of departure from MAR and to adjust for departure from MAR.

In associated methodological work, we will also use the data on the number of follow-up Emails, texts and phone calls needed before an individual responded to explore: 1) the implications of a less intensive data collection regime, and 2) the validity of the assumptions of the repeated attempts model, including that data collected at later attempts are of equal quality.

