### Randomisation and other study procedures

Smokers who respond to the invitation Email and want more information about the study will be referred to a page with more information about the study emphasising that only students who are daily or weekly smokers willing to set a stop date within a month are eligible for the study. Most previous SMS-based smoking cessation studies have used the inclusion criteria - willing to set a stop date with 2 to 4 weeks - facilitating recruitment of a more engaged population both in the intervention and control group and thereby avoiding a larger drop-out of randomised participants before the specified quit date [15,18,23].

By emphasising that participants should be willing to set a stop date this would prevent randomised participants dropping out of the study before completing the intervention. After having read the information about the study all participants gave informed consent to participate by clicking on a link. After informed consent was obtained the participants were guided to a baseline assessment page. The hyperlink contained within the body of the Email is no longer valid after completion of the questionnaire when the responses are stored in the study database. This prevents multiple responses, while allowing the questionnaire to be completed in more than one session if required. After completion of the baseline assessment the students will be asked to provide their telephone number. Then they will immediately receive a SMS that will have to be responded to by writing, ‘start’, in order to confirm that they had stated the right telephone number.

Participants will immediately be randomised to an intervention or waiting list (control) group. Each participant is allocated a number 1 or 2 with equal probabilities using Java’s built in random number generator (java.util.Random). Randomisation is thus fully computerised, does not employ any strata or blocks, and is not possible to subvert, as this and all subsequent study processes are fully automated.

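### Holding the IMOR equal in both arms makes the missing-data grid nearly inert for the odds ratio when attrition is similar, so an arm-specific grid should be added

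*Protocol article*

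**What the plan says.** All of the relevant text is in the Protocol article.

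- **Primary analyses.** Outcomes are assumed missing at random (MAR), and the analysis "will be performed on complete cases only". The abstinence outcomes are reported as odds ratios from logistic regression.
- **Sensitivity analyses.** Departure from MAR is measured by the IMOR. Two restrictions are stated outright: "We will assume that the IMOR is the same in each randomised group", and "we will vary the IMOR over the range 0.5 to 1". An IMOR of 0 (missing = smoking) is added. No reason is given for equality between arms.
- **Sensitivity analyses, continued.** The association between quitting and the number of contact attempts will be examined. A repeated attempts model will then be fitted to estimate, and adjust for, departure from MAR. The article does not say whether that departure may differ by arm.
- **Sample size.** Planning is "with 10% quitting in the intervention group and 5% in the control group", and "If there is 30% attrition in the follow-up measurement the number needed in each group is 677". One attrition figure is given, with no difference between arms.

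**The concern.** The trial's result is a comparison of two arms. If non-responders quit less often than responders, but to the same degree in each arm, both quit rates fall by nearly the same proportion and the odds ratio barely changes. Bias in the odds ratio arises mainly in two ways: the share missing differs by arm, or the link between outcome and response differs by arm. The planned grid holds the second fixed by assumption.

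That second route is plausible here. Allocation is open. The intervention arm receives a core programme of 157 messages, and those who relapse may stop answering. Controls know they will get the programme after the follow-up, so those still smoking have a reason to stay engaged that those who have already quit lack. The direction cannot be known in advance, which is why a sensitivity analysis should vary it.

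At stake is what the trial can say about the robustness of a complete-case result. A table of almost identical odds ratios could be read as reassurance when the analysis had little room to show anything else.

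**Working it through.** **Inputs (Protocol article).** Observed abstinence is 10% and 5%, attrition is 30%, and N = 677 per arm (Sample size). Allocation is 1:1: "Each participant is allocated a number 1 or 2 with equal probabilities" (Randomisation and other study procedures). IMOR values are 0, 0.5 and 1 (Sensitivity analyses).

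**The plan's own figures first.**
- Sample size: the two-proportion formula at 80% power and two-sided 5% gives 435 per arm uncorrected and 474 with the continuity correction, as stated. 474/0.7 = 677.1, matching 677.
- IMOR meaning: odds among the missing = IMOR × observed odds. At 10% observed and IMOR 0.5, 0.5 × 0.1/0.9 = 0.0556, and 0.0556/1.0556 = 5.3%. This agrees with the stated 5%.

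**Method.** For an arm with observed rate p, missing share m and IMOR k:
- p_miss = kp/(1 − p + kp)
- p_arm = (1 − m)p + m·p_miss
- OR = odds of p_arm in the intervention arm ÷ odds of p_arm in the control arm
- Var(p_arm) = [(1 − m) + mk/(1 − p + kp)²]² · p(1 − p)/[N(1 − m)] + (p − p_miss)² · m(1 − m)/N. Dividing by [p_arm(1 − p_arm)]² puts it on the log-odds scale.

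The analysis is unadjusted and the IMOR is treated as known.

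**Common IMOR, 30% missing in each arm**

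| IMOR | Intervention | Control | OR | p |
|---|---|---|---|---|
| 1 | 10.00% | 5.00% | 2.111 | 0.0041 |
| 0.5 | 8.58% | 4.27% | 2.104 | 0.0042 |
| 0 | 7.00% | 3.50% | 2.075 | 0.0046 |
| 2 (not planned) | 12.45% | 6.36% | 2.096 | 0.0043 |

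The planned values move the OR by under 2%. Going above 1 does no more. With 50% missing in each arm the lowest value, at IMOR 0, is 2.053.

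**Arm-specific IMOR, 30% missing in each arm.** The treatment OR among non-responders is the observed OR × (intervention IMOR/control IMOR).

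| (Intervention, control) | OR (95% CI) | p | OR among non-responders |
|---|---|---|---|
| (0.5, 1) | 1.78 (1.07–2.97) | 0.026 | 1.06 |
| (1, 0.5) | 2.49 (1.50–4.15) | 0.0005 | 4.22 |
| (0.4, 1) | 1.71 (1.03–2.85) | 0.038 | 0.84 |
| (0.3, 1) | 1.65 (0.99–2.74) | 0.056 | 0.63 |
| (0, 1) | 1.43 (0.86–2.38) | 0.17 | 0 |
| (0.5, 2), outside the plan's range | 1.38 (0.83–2.30) | 0.21 | 0.53 |

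Example, (0.5, 1). The standard errors of the arm log odds are 0.1526 and 0.2108, so the SE of the log OR is √(0.1526² + 0.2108²) = 0.260. Then z = ln(1.783)/0.260 = 2.22.

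**A weaker observed effect, 9% against 5% (assumption).** Complete cases give OR 1.88, p = 0.017. A common IMOR of 0.5 gives 1.87, and p stays at 0.017. (0.5, 1) gives 1.59 (0.95–2.67), p = 0.08, and implies an OR of 0.94 among non-responders.

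**Unequal attrition (assumption), common IMOR, 10% against 5%.** With 35%/25% missing (intervention/control), the OR is 1.98 at IMOR 0.5 and 1.78 at 0. With 40%/20%, it is 1.87 at 0.5 and 1.53 (0.93–2.52, p = 0.09) at 0.

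**The case against.** A reader might infer that the plan cannot test robustness at all, that the limit of 1 is part of the fault, or that the result is bound to be declared robust. The article supports none of these.

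- **The grid is not the only check.** The repeated attempts model is a separate missing-not-at-random analysis driven by the data, and the article also plans to examine its assumptions. The equality sentence concerns the IMOR only. Whether the model's departure may differ by arm is not stated, and a condensed article may leave that to the full plan. So the model may or may not cover the gap.
- **The limit of 1 is not the cause.** A common IMOR of 2 gives 2.10, as inert as 0.5.
- **The common grid can change the conclusion if attrition differs.** The 40%/20% case shows this. The behaviour that makes unequal IMORs plausible also makes unequal attrition plausible.
- **The corners are strong assumptions.** At the design rates with control IMOR 1, (0.5, 1) already means almost no effect among non-responders and the result stays significant. Losing significance needs a reversed effect among them.
- **30% is a planning allowance.** The article calls it conservative and plans many contact attempts. At an assumed 20% missing per arm, (0, 1) gives 1.65 (p = 0.039) and (0.5, 2) gives 1.59 (p = 0.058). At an assumed 15%, they give 1.77 (p = 0.016) and 1.70 (p = 0.024).
- **No robustness rule is written down.**

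All of this stands and limits the point. What it does not answer is that, with similar attrition, the equal-IMOR grid is close to silent on the odds ratio. At a slightly weaker observed effect (9% against 5%), a roughly null effect among non-responders is enough to lose significance.

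**Conclusion.** The point holds for the IMOR grid under similar attrition, and the equality constraint is the cause. At the design rates and 30% missing per arm, equal IMORs of 0, 0.5 and 1 span odds ratios of 2.08 to 2.11. Unequal values within the plan's own 0.5 to 1 range span 1.78 to 2.49, and (0, 1) gives 1.43.

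The sizes rest on observed rates equal to the design rates, equal attrition of 30%, no covariate adjustment and an IMOR taken as known. They shrink with less attrition. They do not show that the trial's result would be overturned, nor that the sensitivity section as a whole is uninformative. The primary analysis and trial conduct are unaffected. This is a should-fix: an inexpensive improvement to a secondary analysis.

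**What to change.** Keep the equal-IMOR runs and the missing = smoking run as special cases. Add a pre-specified two-way grid in which the IMOR varies separately by arm, for example 0, 0.5 and 1 in each arm, with 2 as a labelled extreme. Over the grid, report the odds ratio with its 95% CI, the tipping point at which the conclusion changes, and the treatment effect that each corner implies among non-responders, so that readers can judge plausibility. Report attrition by arm beside it. State whether the repeated attempts model lets the departure from MAR differ by arm.

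The cost is a few extra runs of a method already planned, some added plan wording and a wider reported sensitivity range. No new data are needed. Recruitment was still open when the article was submitted and analysis starts only after follow-up, so the grid could be fixed before outcomes are seen.
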